# Ethical considerations

## Risks for participants

We expect only minimal risks for children and their caregivers. All study procedures will follow official MOH guidelines for routine child care and child health services. The main purpose of the CDA visits will be to ensure that children are receiving health services developed and scheduled by the MOH. The CDAs **will not** provide medical care to the children, but will refer children to the health clinic when necessary or to the nearest CHA/CHW. The CDAs will give advice on nutritional issues based on MOH guidelines. All of the CDAs will be formally trained in the nutritional and health on the specific messages that they are allowed to communicate. All CDAs will also receive training on the protection of human research participants prior to conducting the study activities.

We consider a minimal psychological risk of embarrassment for the caregivers who have not followed the MOH guidelines for child health visits, and get a reminder from the CDA to bring the child to the clinic. We will minimize this risk by integrating into the CDA training a specific part emphasizing the need for respect and empathy, and avoiding judgmental comments to the caregivers.

We also consider risks for breach of confidentiality to be minimal. All efforts will be made to maintain confidentiality by securely storing the questionnaires and the data from the routine health visits in a safe, locked location (see subsection “Data Security and Management”).

Economic risks are minimal. CDAs will make all efforts to reach the caregivers in moments when they are not working. Caregivers may visit the clinics more often than what they would have been without intervention, which will cost them transportation money. However, no caregiver will be coerced to go and the recommended frequency of routine health care visits will only be within the MOH recommendations for visiting the health facility.

The cognitive/parenting intervention will also have no more than minimal risks. The curriculum for parenting stimulation has been approved by UNICEF and it is largely overlapping with another intervention that UNICEF is implementing in 4 other provinces of Zambia, which has already been approved by local IRBs and by the Ministry of Education. The curriculum is based on basic, safe, uncontroversial and culturally appropriate messages for child development such as basic hygiene messages (handwashing, breastfeeding), quality mother-child interaction messages that encourage the mothers to talk with their child, label objects, sing songs, and make home-made toys (see Study Procedures above). The community-based nature of the group, and the fact that mothers will teach each other rather than having a model strictly imposed or recommended, will further guarantee culturally appropriate practices and discussion. We expect no more than minimal risk for stigma or embarrassment for mothers following practices that were not recommended. The groups are supposed to represent a safe environment amongst peers to discuss and understand the importance of positive practices rather than judgment of negative ones. The CDAs will reinforce this message with the head mother, and will also routinely monitor the groups and signal to the investigators any behavior or dynamic that may generate embarrassment or stigma.

Any unforeseen research-related injury to participants will be borne by the research team.

## Informed Consent

As described above, all caregivers will be informed about the project, and caregiver-child pairs be enrolled only if they provide written informed consent to do so (see Participation Information Sheet and Consent Form attached).

We will ask for a new informed consent before the April 2016 parenting assessment (see Parenting Assessment Information Sheet).

Health workers will be informed about the project in which the interviewer will explain the purpose and rationale of the study and will inform the participants that they will not be paid for participating, they are not obliged to participate, and they can refuse to answer some of the questions. They will be assured of confidentiality regarding any information they provide. They will be asked to sign the consent form, and will be offered the opportunity to receive a copy of the consent form. Only after written informed consent is provided will a participant be permitted to participate in the KII.

## Data Security and Management

## Instrument development

Standardized data collection tools will be designed in TeleForms® (see below for more information) and will be linked to a Microsoft Access database. Instruments will be piloted in the study area and changes will be made as appropriate. These corrections will include alterations for clarity, consistency and spelling mistakes.

## Data capture/paper storage

Identifying information including the woman's full name, location of her home and cell phone number (if applicable) will be kept in a study log book that will be carried by each of the CDA and will be kept separately from the medical information about the study participants. All study forms will only contain study identification numbers and will not contain any identifying information. Field monitors will use standardized forms for all data capture at baseline, midline and endline.

At enrollment, a unique study ID will be given to the caregiver and all forms will use this ID to link the forms together. The study ID will have 5 digits. The first two digits will indicate the cluster (health facility) and the final three digits will be the caregiver’s unique identifier. This will be a continuous number, advancing by 1 for each mother enrolled: i.e. 01001, 01002, 01003, 02001, 02002, 02003, etc.

Data collected at enrollment will include contact information for the mother (address/cell phone). As each mother is enrolled, a timeline will be developed for that mother-infant pair. The timeline will be sent to the CDA and reminders near/around the day of the visit will be given to the CDA to follow-up with the mother.

Data collected at baseline and endline will include information on maternal and child health, weight, height, mid-upper arm circumference (MUAC), as well as neurocognitive assessment (endline only) with standardize questionnaires. At the end of baseline and endline assessment, the data collectors will meet with the field supervisors daily to hand in their paper forms.

For the monthly monitoring, data on children in the intervention arm, including MUAC and presence of danger signs of illness, will be collected. The CDA will meet with a data supervisor every two weeks to hand in all monitoring data on the child.

Field supervisors will review the forms for errors/missing data and will ask the CDA or data collector to fix the errors if possible. Hard copies of the data forms will be taken to the main office (Choma), scanned into a PDF and data captured through the TeleForms program.

All paper files will be stored in the central office in Choma in file drawers, ordered by study ID number. The files will be locked and the field director will have keys to those cabinets. At the end of the study, the paper files or electronic images will be stored up to 5 years past the end of the study.

## Data management

Comprehensive data management and data cleaning will occur in real-time as data is accrued. Over the past 10 years while working in Zambia, we have successfully utilized the TeleForms® system for data verification and entry. This approach offers a high-volume, high-accuracy data capture and management system. Teleforms® enables hand-written text to be translated to computer readable files and then data is entered into a Microsoft® Access database. As Teleforms® includes a data verification system, the need for multiple data entry personnel is eliminated.[53]

A data entry specialist with his/her dedicated scanner, faxed in files, and computer will scan the paper forms, import the faxed forms, and all fields will be verified through the TeleForms® system; this approach acts in a manner similar to a double data entry system. An image file of each paper form is created in scanning. These image files will be backed up to an external hard drive. Data from the TeleForms® system, including the images, and the Access databases will be locked on password-protected computers in the field office. The Access database will be e-mailed as a password-protected file back to the study epidemiologist on a monthly basis.

Monthly data checking will take place with verification of the Access database with the paper forms by the Choma-based data manager. Of all paper records, 10% will be randomly chosen and compared with the Access database each month. Additionally, data cleaning will involve logic checks, range, missing data, and missing form checks. Data queries will be sent from the central office to the data supervisor and the respective field monitor for correction. The data entry specialist and data manager will maintain a data query log; only the data manager in the field will make changes in the Access database.

# Data analysis

We will use the following primary outcomes:

1. Proportion of children with stunting (height-for-age Z-score less than 2 standard deviations below the mean);
2. Child development scores using the INTERGROWTH tool;

Other outcomes of interest include:

1. Proportion of children receiving all age-appropriate vaccines
2. Proportion of children receiving vitamin A supplementation;
3. Number of well-baby visits attended;
4. HOME score;
5. Average time spent reading with the child;
6. Average time spent playing with the child;
7. Proportion of women scoring as depressed, based on the SRQ-20.

We will investigate the relative risk associated with random group assignment as a fixed covariate predicting each outcome using generalized estimating equations (GEE) models that take into account the clustering by health facility. We will use an exchangeable correlation structure in the model.

We will compare baseline characteristics between the two groups that may be related to the outcome, but we expect randomization to have created reasonably balanced groups. Categorical variables will be compared between groups using the chi-square test or Fisher’s exact test if cell sizes are small, continuous variables using t-tests if normally distributed or non-parametric Wilcoxon rank sum tests, if non-normal. We will adjust for confounders as appropriate.

Potential confounders include: maternal education, paternal education, socio-economic status, baseline nutritional status, and presence of food insecurity. The process of randomization should help to balance confounders across the two study arms. Crude and adjusted risk ratios will be presented with 95% confidence intervals in appropriate tables.

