The CDAs will conduct a baseline survey of both control and intervention households which will include: a) basic demographic and socioeconomic status, b) availability of books, toys and other reading material at home, time spent by caregivers reading to the child, as well as time spent by caregivers playing with the child, c) anthropometric screening (weight, height, and MUAC), d) review of vaccinations and child health visits using child health card, e) assessment of maternal or caregiver mental well-being, f) assessment of maternal depression with the SRQ-20 questionnaire, and g) presence of other early childhood development programs in the community. If caregivers report any danger sign during the baseline survey, they will recommend immediate referral to the health facility. If any signs of uncomplicated illness (suggestive of malaria, pneumonia, or diarrhea) are present, the CDA will liaise with the nearest volunteer community health worker (CHW) or community health assistant (CHA), if available in the catchment of the clinic, and refer the child to this person for evaluation. If there is no CHW or CHA in the health zone, the child will be referred to the health center for evaluation. Caregivers will also be asked if they had previously participated to ZamCAT study, and if they would be willing to have the researchers access their baseline data from ZamCAT. Before obtaining permission to review their ZamCAT baseline data, we will obtain written informed consent to access these data.

Households in control health zone clusters will undergo the baseline and endline surveys including an endline assessment of early childhood development. Routine MOH heath facility and community-based activities will continue but none of the aforementioned study interventions will be implemented in the control areas.

Tracking and monitoring system

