**Endline Assessment**

Twelve months after enrollment all children will be visited for a final follow-up interview and assessment. This assessment will be done by a separately trained team of child assessors, and will include the questions asked at baseline as well as an assessment of child development using a standardized test, the INTERGROWTH 21^st^ century assessment tools.

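### Reading time, play time, books/toys items and SRQ-20 are collected at baseline in both arms, but the analysis does not commit to using them as covariates, which may give up precision on these secondary outcomes

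*Protocol*

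**What the plan says.** **Baseline.** Recruitment and baseline survey has the CDAs survey households in both arms. The items include whether books and toys are present in the household, and "time spent by caregivers reading to the child, as well as time spent by caregivers playing with the child". A later item on the same list is the "assessment of maternal depression with the SRQ-20 questionnaire". The same section states that control households have both the baseline and the endline survey.

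**Endline.** Under Endline Assessment, the visit twelve months after enrolment "will include the questions asked at baseline as well as an assessment of child development using a standardized test". Forms are linked by one study ID (Data capture/paper storage), so followed households have paired values.

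**Analysis.** Data analysis lists HOME score, reading time, play time and the proportion of women scoring as depressed on the SRQ-20 among the other outcomes. The GEE model is described in one sentence for all of them: "We will investigate the relative risk associated with random group assignment as a fixed covariate predicting each outcome". Baseline characteristics are then compared between arms, confounders are adjusted for at discretion, and crude and adjusted estimates are reported. The potential confounders named are maternal education, paternal education, socio-economic status, baseline nutritional status and food insecurity.

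**Year two.** The analysis for Objective 10 lists caregiver-child interactions and SRQ-20 depression as outcomes and names no covariates.

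**The concern.** An outcome's own earlier value is often its best single predictor. Here that value is planned for every enrolled household in both arms, yet the section that sets out the model does not say it will be used. The one baseline counterpart of an outcome on the list is nutritional status, which serves stunting. Nothing on the list plays that part for Objectives 3 and 4.

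The adjustment rule also has a different purpose. It treats covariates as possible confounders, considered alongside between-arm comparisons. A prognostic baseline improves precision however balanced the arms look, so a rule based on balance can pass over it.

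Precision matters here because about 15 zones are randomised per arm, stratified on population size and distance to the facility, not on home stimulation or maternal distress. Study interventions says that most of the change in parenting is expected to come from the mother groups, and the stimulation outcomes are where that would show.

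**Working it through.** **Inputs from the protocol (Sample Size Calculations; Determination of clusters and randomization).** 0.5 SD with power 0.9; ICC 0.1; 20 children in each of 30 zones, design effect 2.9; 250 children per arm; 15 zones per arm. No alpha is stated there; 5% two-sided is assumed, in line with the 95% intervals in Data analysis.

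**The protocol's own figure.** Two means, 0.5 SD, power 0.9: 85 per arm before clustering. Design effect 1 + (20 − 1) × 0.1 = 2.9. Then 85 × 2.9 = 246.5 per arm, against 250 stated. It reproduces.

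**Assumed, because the documents give no values for these outcomes.**
- The ICC of 0.1 also holds for reading and play time.
- The effect is a mean difference of 0.3 SD.
- Rho is 0.3, 0.5 or 0.7.
- The zone is the unit of inference.

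Zone size is the enrolment target, 500 / 30 = 16.7.

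**Without the baseline.** Var(difference) = 2 × (0.1 + 0.9/16.67) / 15 = 2 × 0.154 / 15 = 0.0205, so SE = 0.143 SD. Noncentral t with 28 df gives power 0.53 for 0.3 SD.

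**With the baseline, 27 df, two cases.**

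(a) Rho equal at zone and child level: the whole variance is multiplied by 1 − rho².

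(b) Baseline explains within-zone variance only: Var = 2 × (0.1 + 0.9 × (1 − rho²)/16.67) / 15.

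| rho | SE (a) | power (a) | SE (b) | power (b) |
|---|---|---|---|---|
| 0 (none) | 0.143 | 0.53 | 0.143 | 0.53 |
| 0.3 | 0.137 | 0.56 | 0.141 | 0.54 |
| 0.5 | 0.124 | 0.65 | 0.137 | 0.56 |
| 0.7 | 0.102 | 0.81 | 0.130 | 0.60 |

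In case (a) the variance falls by 9%, 25% and 49%. In case (b) it falls by 3%, 9% and 17%, because the between-zone term (0.1 of 0.154) is untouched.

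**At 0.5 SD, the protocol's year-one effect size.** In case (a), power goes from 0.92 to 0.94 at rho 0.3 and 0.97 at rho 0.5. Little is gained if the true effect is that large.

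**Cross-check.** A design-effect calculation with 250/2.9 effective children per arm gives 50% for 0.3 SD without the baseline, and 54%, 62% and 79% at the three values of rho. This agrees with case (a) in direction and size.

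**What this does not cover.** SRQ-20 depression is a proportion analysed by relative risk, so the rho² formula does not carry over and its gain was not computed. HOME score has no stated baseline score; only the books/toys and time items are named, so its gain was not computed either.

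**The case against.** The list of confounders is introduced as examples and adjustment is left to judgement, so these baselines could be added without departing from the protocol. An analysis plan not shown here might do so, and covariate sets for secondary outcomes are often settled there. All of that stands, and it limits the point to a missing commitment. It does not remove it: Data analysis goes as far as a model, an adjustment rule and a named list, and the rule it sets is directed at confounding.

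A reader might infer two stronger things. The first is that the protocol excludes these baselines and compares these outcomes at endline only. The text does not support that, because the list is open and adjusted estimates are promised. The second is that leaving them out biases the arm comparison. It does not: randomisation protects the comparison, and chance imbalance between zones shows up as a wider standard error.

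On size, the objection also has force. Rho could be low, particularly for reading to infants of 6-12 months, where few caregivers may read at all. At rho 0.2 power for 0.3 SD moves only from 0.53 to 0.54, even in case (a). The absence of a power statement for secondary outcomes is ordinary and is not a defect.

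**Conclusion.** The point holds as a low-cost efficiency improvement for secondary outcomes. The protocol collects the baseline values in both arms but does not commit to using them. For reading and play time, the gain in power at an assumed 0.3 SD runs from about 1 point (rho 0.3, within-zone variance only) to about 28 points (rho 0.7, equal at both levels). At rho 0.5 it is between 4 and 12 points. These figures rest on an assumed rho, an assumed effect and the borrowed ICC. They should not be extended to SRQ-20 depression or HOME score. The primary outcomes are outside this point: the neurocognitive assessment is done at endline only, and baseline nutritional status is already named as a potential adjuster.

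**What to change.** In Data analysis, state that:

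- the models for reading time, play time and SRQ-20 depression each include that outcome's own baseline value (for SRQ-20, the baseline score);
- the HOME score model includes the baseline books/toys and time items, described as a proxy because no baseline HOME score is stated;
- these terms are fixed before outcome data are seen and do not depend on the between-arm baseline comparisons.

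In the analysis for Objective 10, use the same baselines for caregiver-child interactions and SRQ-20 depression at year two.

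The cost is wording, about one degree of freedom per covariate, and a simple prespecified rule for missing baseline answers. No new data, visits or participants are needed.

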### 3.1.1. Sampling

A total of five health facilities with a corresponding number of 30 health zones will be selected for the study. All primary caregivers (mothers or other female caregivers) with children between 6 and 12 months of age will be invited to participate in the study for a total of 500 caregiver-child pairs. Details of how participants will be recruited are provided in Section 3.5.

For evaluation purposes, catchment areas of each health facility will be divided along the already established neighborhood health zones with 4-6 zones per clinic. Fifty percent of all zones at each facility will be randomly chosen for the ECD program. The random assignment of zones within each facility to the ECD program will allow us to rigorously assess the program’s impact and effectiveness.

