## Determination of clusters and randomization

Through the recent ZamCAT research efforts, the study team has established a close partnership with district health offices in six districts in Southern Province (Mazabuka, Siavonga, Monze, Choma, Kalomo and Livingstone). In total, 90 facilities were part of the recently completed ZamCAT. Since we aim for a target population of about 500 children, we will choose five facilities with approximately 100-150 children in the 6-12 months age range for the study.

From each of the five facilities, we will randomly select 50% of zones for the program, and use the remaining 50% as a control (comparison) group. The selection of zones will be based on a random number draw. We will select health facilities with six zones each for the study, which means that we expect to have 15 zones in our treatment group and 15 zones in our intervention group. We will randomize health facility zones with stratified randomization with strata based on population size and distance to the health facility; this will help ensure balance in health characteristics of the health zones and populations.

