## Sample Size Calculations

The study is designed to detect increases in standardized child development scores of 0.5 standard deviations with power = 0.9. The main assumptions underlying this calculation are an average group size of 20 children in each of the 30 zones, and an intra-class correlation coefficient of 0.1 (a design effect of 2.9). Similarly, the study is powered to detect an increase in height-for-age z-scores of 0.5 standard deviations in the intervention arm relative to the control arm. We aim to enroll 250 children in each study arm for a total sample of 500 children. In order to account for lost to follow-up, we aim to recruit up to 5% additional children per study arm (262 per arm).

For the year two follow-up assessment, we are powered to detect an increase in standardized child development scores, as measured by the BSID-III, of 0.3 standard deviations with power 0.8.

Sample size for health facility surveys and feeding centers is seven. There will be 10 health workers interviewed (assuming 2 per health facility), 5 national, provincial and district level nutritionists or clinical-care specialists and the feeding sample size for assessment of dietary intake will be all willing and enrolled intervention children (estimate 275).

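### The GEE clusters on 5 health facilities although 30 zones are randomised: false-positive rate about three times nominal, or power of about 74% if corrected at facility level

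*Protocol*

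**What the plan says.** The protocol randomises zones inside facilities. Section 3.1.1 (Sampling) states: "A total of five health facilities with a corresponding number of 30 health zones will be selected for the study", and refers to "The random assignment of zones within each facility to the ECD program". The section Determination of clusters and randomization adds: "We will select health facilities with six zones each for the study", and within each facility "we will randomly select 50% of zones for the program, and use the remaining 50% as a control (comparison) group". This gives three intervention and three control zones per facility, and 15 zones per arm.

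Sample Size Calculations follows the same structure. It assumes "an average group size of 20 children in each of the 30 zones, and an intra-class correlation coefficient of 0.1", with a design effect of 2.9.

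The Data analysis section departs from it. Every outcome is to be analysed with "generalized estimating equations (GEE) models that take into account the clustering by health facility" and an exchangeable working correlation. Data capture/paper storage uses the same label for the study ID: "The first two digits will indicate the cluster (health facility". The remaining three digits of the ID number the caregivers, so the ID has no zone code.

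**The concern.** The unit that determines the error of the arm comparison is the unit that was randomised, here the zone. The analysis section names the facility, which is the block within which zones are allocated. Two problems follow, depending on the standard error used.

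- **Robust (sandwich) standard error.** Whole zones lie inside facilities, so a facility-level sandwich does absorb the correlation within zones. However, it is estimated from only five clusters, which biases it downwards and makes a normal reference far too optimistic.
- **Model-based standard error.** An exchangeable correlation across a whole facility treats children from different zones of that facility as being as alike as children from the same zone. The between-zone variance is then left out of the arm contrast.

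The model is prescribed for both primary outcomes and all seven other outcomes, so the fault would carry into every p-value and confidence interval it produces. The analysis also contradicts the sample size calculation, which earns its power from 30 clusters.

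**Working it through.** **Inputs.** 5 facilities with 6 zones each, 3 per arm (Sampling; Determination of clusters and randomization). 250 children per arm, so m = 500/30 = 16.7 per zone; the sample size section assumes 20. ICC 0.1, effect 0.5 SD, power 0.9 (Sample Size Calculations). Two-sided 5% is assumed from the 95% confidence intervals in Data analysis.

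**1. The plan's own figure.** Unclustered n per arm = 2(1.96 + 1.2816)²/0.5² = 84.1, rounded up to 85. Design effect = 1 + (20 − 1) × 0.1 = 2.9. 85 × 2.9 = 246.5, against 250 stated. The figure reproduces, with zones as the clusters.

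**2. True standard error of the arm difference.** With total variance 1, a zone mean has variance 0.1 + 0.9/16.7 = 0.154. With 15 zones per arm, SE = √(2 × 0.154/15) = 0.143 SD.

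**3. Facility-clustered GEE, robust SE.** In the balanced case the estimate is the mean of five within-facility differences. The sandwich variance is their sum of squared deviations divided by 25, which is 4/5 of the unbiased value on average. Type I error = 2P(t₄ > 1.96 × √0.8) = 2P(t₄ > 1.753) = 15.4%, or 3.1 times nominal. The zone ICC cancels out. The mean robust SE is 84% of the true one (0.84 × 0.143 = 0.120), and a nominal 95% interval covers about 84.5%.

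**4. Facility-clustered GEE, model-based SE.** The arm contrast is judged against √(2/250) = 0.089. Type I error = 2P(Z > 1.96/√DE), with DE = 1 + 15.67 × ICC:

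| Zone ICC | DE | Type I error |
|---|---|---|
| 0.02 | 1.31 | 8.7% |
| 0.05 | 1.78 | 14.2% |
| 0.10 | 2.57 | 22.1% |

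At 20 children per zone and ICC 0.1 (DE 2.9) it is 25.0%.

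**5. Simulation under no effect.** In 2,000 Gaussian trials per scenario (zone ICC 0.02 to 0.10, facility ICC 0 to 0.05), the facility-clustered GEE rejected in 14.5% to 16.9% with robust SE and 9.8% to 23.2% with model-based SE. A second set of 1,500 trials per scenario, including unequal zones and variance split between facility and zone, gave 13.3% to 16.1% with robust SE for the continuous score. For stunting (36% prevalence assumed, from the Summary) it gave 17.2% with robust and 9.3% with model-based SE.

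**6. Correcting at facility level.** Multiplying the variance by 5/4 and using t on 4 df returns 5.0%. Power at 0.5 SD, with non-centrality 0.5/0.143 = 3.49 and critical value 2.776, is 74%.

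**7. Analysing the 30 zones.** Power with the same non-centrality is 92.0% on 28 df, and 91.7% on 24 df (30 zones − 5 facilities − 1 arm term). The uncorrected sandwich is still somewhat liberal. Without facility effects it gives 2P(t₂₈ > 1.96 × √(28/30)) = 6.9%; with facility fixed effects, 2P(t₂₄ > 1.96 × √(24/30)) = 9.2%. Zone means with facility as block and t on 24 df rejected in 4.5% to 5.2% of the 2,000-trial simulations.

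**The case against.** The best counter-argument is that the protocol names neither the variance estimator nor the reference distribution. A SAP that is not shown might specify a small-sample correction, in which case the intervals would not be too narrow. This stands to the extent that the factor of three is conditional on an uncorrected robust SE. It does not rescue the stated rule: a corrected five-facility test has 4 df and about 74% power, which contradicts the stated 90%. Nor is the clustering unit a detail left open for the SAP, because the protocol fixes it.

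Three smaller points also stand:

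- With robust SEs the inflation comes only from having five clusters. Unrepresented between-zone variance is the mechanism for model-based SEs.
- The study ID shows a mislabelled cluster, not lost data. Zone may be held elsewhere on the forms, and staff need to know it to deliver the intervention.
- 24 df holds for facility blocks alone. The protocol also stratifies by population size and distance to the facility, and adjusting for those strata lowers the df.

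The trial aims at feasibility and preliminary impact, and the children can be analysed by zone without any change in conduct. That makes the fault easy to repair, but the prescribed analysis still does not match the design.

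**Conclusion.** The concern holds. The protocol randomises and powers on 30 zones, then prescribes an analysis clustered on the five blocks. As written, the plan loses either error control or planned power. Type I error is 15.4% with the usual robust SE, and about 9% to 22% with model-based SE for a continuous score at zone ICCs of 0.02 to 0.10. If corrected at facility level, power is about 74% instead of 90%. The analytic figures assume equal zones and a continuous outcome at two-sided 5%; simulations with unequal zones and with binary stunting point the same way for the robust SE. The power figures use the protocol's ICC of 0.1 and 250 children per arm. This should be corrected before analysis, because it affects both primary outcomes.

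**What to change.** In Data analysis, replace the health facility with the health zone as the GEE cluster, and state that the zone is the unit of randomisation. Include facility as a fixed effect, together with any other stratum used in the randomisation. Specify a small-sample-corrected variance with a t reference (24 df with facility effects alone, fewer if further strata are added), or an analysis of zone-level summaries with facility as block. The correction is needed because the uncorrected zone-level sandwich still rejects in about 7% to 9% of null trials by the formulas above.

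In Data capture/paper storage, stop calling the facility the cluster, and require a zone code on every form or in the database.

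The cost is one or two sentences and one variable. No more children are needed: power at 0.5 SD stays near 92%. Confidence intervals will be wider than those from the uncorrected facility analysis, with close to nominal coverage.
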